## 6.2 Statistical analysis

### 6.2.1 Pilot study

The relative risk of a syncope occurring on the Erigo or the tilt table as well as the odds ratio will be calculated according to the statistics recommended.

### 6.2.2 Randomized controlled trial

Fifty patients will be enrolled in this study.

Sample size calculation

The sample size was estimated according to the main criterium measured by CRS and based on a 6-week follow-up on the effect of the standard therapy in 12 minimally responsive/apallic patients. The differential value of the CRS before and after a 6-week standard therapy showed a mean value improvement of 6.5 points with a variance of 12.3 (SD=3.5). An additional improvement of the CRS by 3 points is expected as results of the study planned here. This means that on the average an additional improvement in half of the evaluated items of the CRS is expected.

The sample size was estimated in order to check by inference statistical means the hypotheses of an interval-scaled feature ([10]) if the prerequisite of a corresponding normal distribution is fulfilled. The values  $\alpha = 5\%$  two-sided, power = 80% result in a group size of 22 patients for each of the two groups with the expected increase of CRS by 3 points. A difference of at least 3 points between the

two groups can be established as significant in case of a variance of the differential values (before/after treatment) of the CRS of  $3.5^2 = 12.3$  and in group size of  $n=22$  with an error probability of 0.5 and a power of 0.8. In addition the number of therapy drop-outs was so determined that the required number of patients will still be achieved even after subtracting an expected drop-out rate of 10%. Thus, a total of 25 patients as group size is included in the randomization procedure.

A 2-way analysis of variance (ANOVA) will be performed to statistically analyse the primary outcome parameter CRS-R. If the assumptions of homogeneity of variances or normal distribution are disproven, nonparametric tests will be used.

In case patients withdraw from the study at the wish of the caretaker, the patient will be referred to in the log book as “intention-to-treat”.

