**Therapeutic consequences must be documented, for example drug treatment, exclusion from the study.**

An event is termed an “unexpected adverse event“ in connection with the tested medical product (MP) if its nature or severity does not agree with the known data on the safety and tolerance of the MP.

**Causality:** The following definitions are used to determine the connection between the use of a medical product (MP) and the AE:

- **Safe:** A reaction that follows within a reasonable temporal course after use of the test product, that follows a known or expected response pattern to the suspected test product, and disappears when removed or when the dosage is reduced and recurs with repeated exposure.
- **Probable:** A reaction that follows within a reasonable temporal course after use of the test product, that follows a known or expected response pattern to the suspected test product, and disappears when removed or when the dosage is reduced and cannot be explained by the known features of the patient’s clinical state.
- **Possible:** A reaction that follows within a reasonable temporal course after use of the test product, that follows a known or expected response pattern to the suspected test product, but which can be easily elicited by a number of other factors.
- **No connection:** A reaction for which there is sufficient information available to assume that there is no connection with the test product.
- **Unassessable:** It is not possible to assess a connection.

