## **10 Termination criteria**

Individual

- If the systolic blood pressure falls by 20 mmHg or the diastolic blood pressure by more than 10 mmHg during the uprighting of the patient, therapy is continued at the next lowest tolerated angle of uprightness (30 or 50 degrees).
- The same procedure is followed with symptoms of a presyncope (tachypnoe, paleness, increased sweating...).
- Therapy is immediately terminated if the pulse falls below 40 beats/min or rises above 140 beats/min.
- Arterial hypotension (<80 mmHg).
- The occurrence of a new disease or complication of the primary illness that makes a continuation of the study impossible.
- Legal proxy withdraws participation agreement.

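### The protocol does not separate stopping device therapy from leaving the study, so follow-up and analysis of all randomised patients as allocated are not secured

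*Protocol*

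**What the plan says.** - **Section 6.2.2, withdrawals.** "In case patients withdraw from the study at the wish of the caretaker, the patient will be referred to in the log book as" intention-to-treat. The term appears nowhere else in the protocol. It is not defined as an analysis population, and no other reason for stopping receives it.
- **Section 6.2.2, sample size.** The allowance counts patients who drop out of therapy ("In addition the number of therapy drop-outs was so determined"). Its stated purpose is this: "the required number of patients will still be achieved even after subtracting an expected drop-out rate of 10" per cent. It takes 25 randomised per group down to 22.
- **Section 9.3.1, adverse events.** "Therapeutic consequences must be documented, for example drug treatment, exclusion from the study". Leaving the study is thus named as one possible consequence of an adverse event.
- **Section 10, individual termination criteria.** One list holds a reduction of the tilt angle, termination of therapy on pulse limits, proxy withdrawal, and this item: "The occurrence of a new disease or complication of the primary illness that makes a continuation of the study impossible". It does not say which items end treatment and which end follow-up.
- **Section 6.1, randomisation.** A drop-out is replaced by the next patient, who takes the same assignment. The paragraph on the randomised trial says that its study procedure is that of the pilot.
- **Sections 4.2 and 7.5, schedule.** The CRS-R is taken before therapy and at 3 and 6 weeks. No condition is attached about having completed therapy.

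**The concern.** Intention-to-treat is a rule about analysing every randomised patient in the assigned group. Here it marks one withdrawal reason, and the one in which further ratings may no longer be allowed. Patients whose therapy ends for illness, complication or an adverse event are not mentioned, although consent may still stand and some could still be rated. The CRS-R is a rating that does not need the device; section 4.2 says it is not taken during the interventions.

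The sample-size text treats a therapy drop-out as a patient lost to the comparison, and the substitution rule points the same way. A trial team following these sections could stop rating such patients, replace them, and compare those who remain.

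The primary CRS-R comparison is at stake. The protocol expects a fall in blood pressure on the tilt table (section 4.2.2) and less syncope on the Erigo (sections 5.3 and 11.1.1). Poor tolerance could therefore differ by arm. Stops for new disease or complication plausibly go with poorer recovery. If both hold, the patients left in each arm are no longer comparable.

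**Working it through.** **1. The plan's own figure.** Inputs from section 6.2.2: difference 3 points ("An additional improvement of the CRS by 3 points is expected"), SD 3.5 (the reference patients "showed a mean value improvement of 6.5 points with a variance of 12.3 (SD=3.5"), alpha 5% two-sided, power 80%.

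n per group = 2 × (1.960 + 0.842)² × 3.5² / 3² = 21.4, rounded up to 22. This agrees with the stated figure ("two-sided, power = 80% result in a group size of 22 patients for each of the two groups"). Then 22 / 0.90 = 24.4, rounded up to 25. Both figures reproduce. With a two-sample t-test, 22 per group gives 79.3% power. The arithmetic is sound; the issue is what the step from 25 to 22 assumes, namely that a therapy drop-out supplies no outcome.

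**2. The passages side by side.**

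| Section | What happens when therapy stops |
|---|---|
| 6.2.2, sample size | Patient is subtracted from the number needed |
| 6.2.2, log book | Label given only for withdrawal at the caretaker's wish |
| 6.1 | Drop-out is substituted |
| 9.3.1 | Study exclusion given as an example of a consequence |
| 10 | Ending therapy and ending participation share one list |
| 4.2, 7.5 | CRS-R still due at weeks 3 and 6 |

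The last row fits badly with the first and third. No passage says which prevails.

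**3. Possible size of the bias (assumed figures).** Let the mean change over all randomised patients be 6.5 (tilt table) and 9.5 (Erigo). Let pT and pE be the proportions stopped, and d the deficit of stopped patients against completers in the same arm. An arm mean equals its completer mean minus p × d, so:

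completer difference = (9.5 + pE × d) − (6.5 + pT × d) = 3 − (pT − pE) × d

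The split 16% vs 4% is 4 and 1 of 25, or 5 of 50, which matches the planned overall rate of 10%. The split by arm and d are assumptions.

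| pT | pE | d | Completer difference |
|---|---|---|---|
| 10% | 10% | any | 3.00 |
| 15% | 5% | 3 to 5 | 2.70 to 2.50 |
| 16% | 4% | 3 to 5 | 2.64 to 2.40 |
| 4% | 16% | 3 to 5 | 3.36 to 3.60 |

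At 22 per group and SD 3.5, t-test power is 79.3% for 3.0, 68.6% for 2.64 and 60.3% for 2.40.

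**4. What keeping everyone does to power.** Here 3 points is instead taken as the effect in patients who complete therapy, and the 10% who stop keep a fraction f of it. The difference is 3 × (0.9 + 0.1f). With all 25 per group rated and SD 3.5, t-test power is 84.4% for f = 1 (3.00 points), 80.5% for f = 0.5 (2.85) and 76.2% for f = 0 (2.70).

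**The case against.** A reader might infer that patients stopped for circulatory or medical reasons lose their week-3 and week-6 CRS-R and are left out of the ANOVA. The documents do not say so. The schedule is unconditional, section 6.2.2 excludes nobody from the ANOVA by name, and the analysis set may be defined in a statistical analysis plan that is not at hand. This objection stands.

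A reader might also infer that most circulatory events end participation. Section 10 does not support that. After a blood-pressure fall or presyncope, therapy continues at a lower angle. The pulse rule ends therapy, a word that sections 7.1 and 7.5 also use for one session. The hypotension item states no consequence. More such events on the tilt table need not mean more exits, and the protocol gives a single drop-out rate of 10%. This stands too. The clearer routes out are illness or complication, exclusion after an adverse event, and proxy withdrawal.

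Other limits also hold. Some patients too ill to continue may not be ratable. Section 9.3.1 gives an example of something to document, not a rule that adverse events end follow-up. The log-book sentence may simply mean that a patient withdrawn by the proxy still counts as randomised.

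What survives is in the text itself. The protocol attaches intention-to-treat to one withdrawal reason, plans therapy drop-outs as subtracted and, by cross-reference, substitutes them. That is a rule fixed badly, not a detail left for later; a later analysis plan covering everyone as randomised would have to override it.

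**Conclusion.** The concern holds in a limited form: stopping therapy and leaving the study are run together, and the current wording does not secure outcome collection and analysis for all randomised patients as allocated. It does not establish that any patient will lose ratings or be dropped from the analysis.

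The size cannot be known from the protocol. In the illustrated case, a completer comparison would lose about 0.4 to 0.6 of the planned 3 points. This rests on unequal stopping by arm and on stopped patients recovering less well. The direction depends on which arm has more stops: more on the tilt table works against the Erigo, more on the Erigo works in its favour. The sample size of 22, raised to 25 per group, is not in question.

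**What to change.** In section 6.2.2, replace the log-book sentence with: *All randomised patients are analysed in the group assigned. Ending device therapy for any reason does not end the scheduled week-3 and week-6 assessments, unless the proxy withdraws consent to further data collection.* Record withdrawal from therapy and withdrawal from data collection as separate items.

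Reconcile sections 6.1, 6.2.2, 7.5, 9.3.1 and 10 so that they agree on which events end therapy and which end study participation. No clinical stopping criterion needs to change for this.

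The cost is protocol wording and a few more ratings at visits already scheduled. The estimated effect may be somewhat diluted by patients who stopped early. On the assumptions in step 4 of the working, power with all 25 per group would lie between about 76% and 84%, close to the planned 80%.

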### 6.3 Inclusion criteria

- Condition following traumatic intracranial injury, hypoxic brain injury, intracerebral bleeding or ischemic stroke
- Apallic syndrome / minimally responsive state according to the CRS revised

In the main study the category of patients with hypoxic brain injury will be restricted to minimally responsive patients, since various studies have shown a poor prognosis for apallic patients after a hypoxic brain injury ([11]). Thus their inclusion in a therapy study does not appear to be expedient. The acute event is not older than 6 months. The patient has so far been mobilized for less than 30 minutes in a standing position. The patient is not younger than 28 and not more than 70 years old.

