#### 4.2.2 Secondary outcome measure

To evaluate an immediate stabilizing effect of the Erigo therapy on circulation, the following cardiovascular parameters will be measured:

- Heart rate
- Blood pressure; the Hypothesis: difference between initial value and the value after the intervention phase is greater for the tilt-table therapy (drop in blood pressure during tilt-table therapy)
- Oxygen saturation; the Hypothesis: increased oxygen saturation during Erigo therapy
- As co-variables the duration of verticalization (max. of 30 min per therapy session), and the degree of the maximum tilt will be analyzed

To evaluate a clinically unapparent effect on vigilance the following parameters will be measured:

- Skin conductance as reaction to command (should increase during Erigo therapy)
- Heart rate variability (should increase during Erigo therapy)
- Head control/movement during therapy (better during Erigo therapy)

The change in muscle tone or spasticity will be measured before the intervention, after the intervention, and after a 3 week follow-up period using the

- Ashworth-Scala.

To better compare the results of this study with results of international studies, the following parameters will be measured:

- at study onset: GCS (Glasgow Coma Scale)
- at discharge: GOS (Glasgow Outcome Scale)

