## 6.1 Method of randomization

### 6.1.1 Pilot study

**Allocation procedure:** All patients will receive one therapy session on the Erigo and one therapy session on the tilt table. The sequence of both therapies will be applied in random order. Consequently, patients will be randomized in one of two groups (1 = tilt table - Erigo, 2 = Erigo – tilt table) by means of a computer-generated randomization list.

**Concealment:** The computer-generated randomization list will be prepared by the Department for Medical Data Evaluation of the Schön Kliniken. **Study procedure:** Each patient who meets the inclusion or exclusion criteria will be immediately and consecutively reported on to the statistician or his/her representative. He/she will inform those involved in the project about each consecutive test person's group within the fixed order (descending) by telephone or in person and will note the patient data (Surname, Name, Date of birth) on the randomization list. The first patient will receive the number 1, the second patient, the number two, and so on, and group allocation will be recorded. A log book will be kept on the assignments and will be available for inspection at the end of the study. In this way the secrecy of the as yet not applied randomization order is ensured. A drop-out will be substituted by the next test person in chronological order, but the assignment to therapy and control group will be kept the same as that of the drop-out.

Randomized controlled trial

**Allocation procedure:** The study participants will be assigned to one of two groups: **Group 1 = treatment with the tilt table, Group 2 = treatment with the Erigo.** The randomized stratified grouping is performed in accordance with two criteria, which are expected to have an effect on the outcome of the patients: the original diagnosis (traumatic vs. non-traumatic) and severity of the disorder of consciousness according to the CRS at study begin (apallic vs minimally responsive) ([9]).

**Non-disclosure conditions and study procedure** are the same as in the pilot study.

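### Patients enter at any time up to 6 months after the event, but time since event is neither stratified nor a term in the stated CRS-R analysis: possible lost precision and uncorrected chance imbalance, not bias

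*Protocol*

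**What the plan says.** - **Entry window.** Section 6.3 requires that "The acute event is not older than 6 months". No minimum time since the event is given. A further criterion limits earlier mobilisation: "The patient has so far been mobilized for less than 30 minutes in a standing position".
- **Stratification.** For the controlled trial, section 6.1 stratifies on two criteria "which are expected to have an effect on the outcome of the patients": traumatic or non-traumatic origin, and apallic or minimally responsive state by CRS at the start. Time since event is not among them.
- **Primary analysis.** Section 6.2.2 states: "A 2-way analysis of variance (ANOVA) will be performed to statistically analyse the primary outcome parameter CRS-R". The two factors are not named and no covariate is mentioned. The fallback is equally bare: "If the assumptions of homogeneity of variances or normal distribution are disproven, nonparametric tests will be used".
- **Covariates elsewhere.** Section 4.2.2 does name some, but under the cardiovascular secondary outcomes: "As co-variables the duration of verticalization (max. of 30 min per therapy session), and the degree of the maximum tilt will be analyzed".
- **Planning data.** Section 6.2.2 uses 12 patients on standard therapy whose CRS rose by a mean of 6.5 points over 6 weeks, with an SD of change of 3.5. The effect sought is a further 3 points, with 22 per group before drop-out and 25 after. The time since event of those 12 patients is not stated.

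**The concern.** The trial looks for a 3-point increment on top of a background gain that averaged 6.5 points in the planning data. It does so in patients who may be anywhere from shortly after the event to 6 months after it. If the background gain depends on how long ago the event was, two things follow. That part of the variation stays in the error term and costs power. And with about 22 evaluable patients per arm, the arms can differ by chance in time since event, which moves the CRS-R difference in a way the stated analysis does not remove.

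The event date has to be known to apply the 6-month criterion, so the variable is already available at baseline. The choice also needs to be made in advance, because an adjustment added after an imbalance has been seen is open to challenge.

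**Working it through.** **Inputs.** From section 6.2.2: difference 3, SD of change 3.5, two-sided alpha 5%, power 80%, 22 per group, drop-out 10%. Assumed: r, the correlation between time since event and CRS-R change beyond the stratification factors, taken over 0 to 0.5.

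**1. The plan's own figure.** n per group = 2 × (1.960 + 0.842)² × 3.5² / 3² = 21.4, rounded up to 22. With drop-out, 22 / 0.9 = 24.4, rounded up to 25. Both stated figures reproduce. The normal approximation gives 81.1% power at 22 per group. The noncentral t with 42 df gives 79.3%, which is the reference used below.

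**2. Power with the covariate.** Two effects work against each other.
- The residual SD falls to 3.5 × √(1 − r²).
- The variance of the treatment difference rises because the covariate is itself imbalanced by chance. With 44 patients and a roughly normal covariate, the expected factor is 1 + 1/40 = 1.025. One error df is also lost, leaving 41.

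The standard error is 3.5 × √(1 − r²) × √(2/22 × 1.025), and power comes from the noncentral t with 41 df and a difference of 3:

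| r | Residual SD | SE of difference | Power |
|---|---|---|---|
| unadjusted | 3.50 | 1.055 | 79.3% |
| 0 | 3.50 | 1.068 | 78.3% |
| 0.1 | 3.48 | 1.063 | 78.7% |
| 0.2 | 3.43 | 1.047 | 79.9% |
| 0.3 | 3.34 | 1.019 | 82.0% |
| 0.4 | 3.21 | 0.979 | 84.9% |
| 0.5 | 3.03 | 0.925 | 88.6% |

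The variances break even where 1.025 × (1 − r²) = 1, that is r = √(1 − 1/1.025) = 0.156. With the lost df, break-even is near r = 0.16.

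**3. Shift from chance imbalance.** In units of the covariate's SD, the difference in arm means has standard error √(2/22) = 0.30. The unadjusted CRS-R difference moves by r × 3.5 × imbalance.
- One-SE imbalance: 0.2 × 3.5 × 0.3015 = 0.21 points at r = 0.2, and 0.53 at r = 0.5.
- 1.96-SE imbalance: 0.41 points at r = 0.2, and 1.03 at r = 0.5.

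**4. Conditional error rate.** An imbalance above 0.5 SD has probability 2 × [1 − Φ(0.5 / 0.3015)], about 10%. Given an imbalance of exactly 0.5 SD, the shift is 0.5 × r × 3.5, the conditional standard error is 1.055 × √(1 − r²), and the rejection limit is 2.018 × 1.055 = 2.13. The conditional type I error is then about 6.0% at r = 0.3, 7.1% at 0.4 and 8.5% at 0.5. At an imbalance of 0.3 SD it is below 5% (4.3%, 4.3% and 4.1%). Over all possible randomisations the rate stays nominal.

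**The case against.** **Covariates are usually settled in the analysis plan, which is not shown.** This has force: the two ANOVA factors are unnamed, and a separate plan could add terms. But the protocol does name its primary method, a 2-way ANOVA has no continuous covariate, and the sponsor listed co-variables in the protocol where it wanted them. The point is an improvement to a stated method; it does not rest on a missing detail.

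**Nothing in the protocol says time since event predicts CRS-R change.** This stands. Section 6.1 names two factors expected to matter, and this is not one of them. The value of r is wholly assumed, and any part of it shared with diagnosis or severity does not count. The limit on earlier standing may also narrow the real spread of entry times, although it restricts mobilisation and not time.

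**The sample size already carries this variation.** Also true. The SD of 3.5 is unadjusted, so adjustment would add precision to the design as planned; it does not make good a shortfall.

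Three stronger readings are tempting, and the documents support none of them.
- A reader might infer from the 6.5-point mean gain that the rate of recovery is the main source of variation. A mean does not show what drives the SD, and a gain common to both arms cancels in their difference.
- A reader might infer that the comparison is biased or its type I error inflated. Randomisation rules this out unconditionally.
- A reader might infer that adjustment can only help. If r is below about 0.16, it costs a little power.

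**Conclusion.** The point holds as a modest improvement to a named method. Entry is open up to 6 months after the event, and time since event is in neither the stratification nor the stated primary analysis.

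What is at stake is conditional. The gain over 79.3% is negligible at r = 0.2 (0.6 percentage points), becomes useful at r = 0.3 (2.7 points) and is clear at r = 0.5 (9.3 points). If the covariate is unrelated to outcome, the loss is about one point. An unlucky but ordinary imbalance could move the estimate by 0.2 to 0.5 points of the 3 sought, for r = 0.2 to 0.5.

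These figures rest on the assumed r, on an SD taken from 12 patients whose time since event is not stated, and on a roughly linear relation. They price the time term alone, not the other terms of the model proposed below.

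**What to change.** In section 6.2.2, pre-specify the primary CRS-R analysis as a linear model with:
- treatment;
- baseline CRS-R;
- the two stratification factors;
- time from the acute event to randomisation, as a continuous variable in days or log days, with the scale fixed in advance.

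Report the distribution of time since event by arm. If the nonparametric fallback is kept, state whether these covariates carry over to it.

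The randomisation scheme stays as it is; a third factor on top of the existing four strata would leave sparse cells with 50 patients. For the time term the cost is one degree of freedom, with no new data and no extra patients. The downside is a loss of about one power point or less if it proves unrelated to outcome.
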